### Study visits and data collection

An overview of timing of enrolment, interventions and assessments in the study is provided in Table 1.

**Table 1 Tab1:** Overview of timing of enrolment, interventions and assessments in the CRISTAL study

		STUDY PERIOD									
**TIMEPOINTS**		**Screening**	**Baseline run-in** (within 1 week after screening)	**Randomisation**	**Training 780G HCL system or masked CGM** (within 1 week after run-in)	**Study visit 1 ** (if screening < 8 weeks)	**Study visit 2**	**Study visit 3**	**Study visit 4**	**Study visit 5**	**Delivery ** **and early postpartum**
**ENROLMENT**	**Eligibility screen**	X									
	**Informed consent**	X									
	**Allocation**			X							
**INTERVENTIONS**	***(masked) CGM for 10 days***		X								
	***(masked) CGM for 21 days***					X	X	X	X	X	
	***780G HCL system***				X	X	X	X	X	X	X
**ASSESSMENTS**	***Outcomes collected from medical records***:										
	Demographic data	X									
	Medical and obstetrical history	X									
	***Clinical and biochemical outcomes***:										
	Physical examination	X				X	X	X	X	X	
	HbA1c	X				X	X	X	X	X	
	Future analyses of new bio-markers and metabolomics	X				X	X	X	X	X	
	CGM metrics		X			X	X	X	X	X	X
	(S)AEs and DDs		X			X	X	X	X	X	X
	Other relevant health data	X				X	X	X	X	X	X
	C-peptide										X
	Future analyses of new bio-markers and metabolomics in umbilical cord blood										X
	Sum of skinfolds										X
	Neonatal body fat mass										X
	***Patient-reported outcomes***:										
	Self-administered questionnaires	X				X	X	X	X	X	
	Data for health-economic evaluation	X				X	X	X	X	X	X
	Medication use	X				X	X	X	X	X	X

HCL hybrid closed-loop; CGM continuous glucose monitoring; HbA1c glycated haemoglobin; (S)AEs (serious) adverse events; DDs device deficiencies.

#### *Baseline run-in phase*

Baseline CGM data (from the Guardian™ 3 or 4 CGM) of all participants will be collected during ten days. Only participants with a glucose monitoring method other than the Guardian™ 3 or 4 CGM will be requested to wear a masked Guardian™ 3 CGM in addition to their current glucose monitoring method. When using a masked Guardian™ 3 sensor, SMBG will be required at least twice a day for retrospective CGM calibration purpose.

#### *Training*

Within one week after the run-in phase, participants randomised to the intervention group will receive structured education on use of the 780G HCL system (ambulatory or with a short hospitalisation in line with normal routine). Participants allocated to the control group will be educated on the use of the masked Guardian™ 3 CGM, if applicable.

#### *During the screening visit and different study visits*

Study visits will be planned for participants of both groups at different time points in pregnancy: around 9 (if screened < 8 weeks), 14, 20, 26, and 33 weeks. The last study visit at 33 weeks can be performed earlier at 31–32 weeks if preterm delivery is expected. At each visit, a physical examination (with measurement of weight, blood pressure, and once height at screening) and blood collection (to measure HbA1c and for long-term storage in the biobank to allow future analyses of new biomarkers and metabolomics) will be performed. The glucose monitoring and insulin therapy data will be collected and reviewed to adjust the therapy, if needed. Differences in glycaemia between both groups will be evaluated by similar (masked) CGM data collected during 21 days at 9–12 (if screened < 8 weeks), 14–17, 20–23, 26–29, and 33–36 weeks. In addition, self-administered questionnaires, as listed above, will be completed at every study visit. Additional (tele)consultations can be performed according to need in between routine visits.

#### *Delivery and early postpartum*

At delivery and in early postpartum, based on the advice of the treating physician, the 780G HCL system can be continued, temporarily switched to open-loop or substituted by an insulin drip. If HCL is continued, increasing the glycaemic target to 6.1 or 6.7 mmol/L (110 or 120 mg/dL) and the ICR with at least 50% during the (end of the) dilation phase and delivery will be advised as a rapid decrease in insulin resistance is expected after delivery of the placenta [40]. After delivery, umbilical cord blood will be collected for measurement of C-peptide and storage in the biobank to allow future analyses of new biomarkers and metabolomics, if informed consent is provided. Neonatal skinfold thickness measurement will be performed within 72 h after birth, after giving informed consent, by trained study staff using a Harpenden skinfold caliper, as previously described in the HAPO study [41]. Skinfolds will be measured twice consecutively at the triceps, subscapular, and flank. The mean measured value at each site will be used to calculate the sum of skinfolds. Neonatal body fat mass will be determined according to a validated formula [42, 43].

### Statistics

#### *Sample size*

The sample size is determined to have about 90% power for the primary and three key secondary outcomes. To this purpose, at least 92 patients in total will be randomised. The sample size calculation was performed for these four outcomes separately, considering a Bonferroni correction for multiple testing to guarantee a 5% two-tailed family-wise significance level, and withholding the largest sample size. Calculations were performed for showing a time-averaged difference between the two groups over four longitudinal measurements [44]. A correlation of 0.6 was assumed between repeated measurements and a 20% loss to follow-up during the study was anticipated. For the primary outcome, the sample size was determined to detect an absolute between-group difference in mean TIR of 10% during pregnancy, assuming a SD of 13% for the TIR [22]. The power to show a difference of 1.1% between both groups for TBR, assuming a SD of 1.6% equals 91%. The power to show a difference of 1.6% between both groups for overnight TBR, assuming a SD of 2.5%, equals 87%. The power to show a difference of 15.2% between both groups in overnight TIR, assuming a SD of 18.4%, equals 97% [20]. After randomisation of approximately 50% of participants, a blinded sample size recalculation will be performed to re-estimate variances and correlations [45]. The sample size will be adjusted if needed to achieve the anticipated power.

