### Randomisation

Randomisation will be performed centrally by software and a randomisation algorithm developed by I Biostat. Participants will be randomised 1:1 to either the 780G (intervention) or SoC (control) group. Deterministic minimisation of variation will be used based on the following baseline characteristics: study centre, baseline HbA1c (locally determined at screening) stratified according to HbA1c < 53 vs. ≥ 53 mmol/mol (< 7 or ≥ 7%), and method of insulin delivery (MDI or insulin pump) [39].

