#### *Data analysis*

Analyses will be performed according to intention-to-treat as well as per protocol. Clinical and demographic data at baseline will be summarised in a table using frequencies with percentages, mean values with SD or medians with the interquartile range (IQR). A linear mixed model for repeated measurements will be used for the primary outcome analysis, with TIR as response variable, and group, time point of measurement, stratification factors baseline HbA1c and method of insulin delivery, and finally baseline TIR as main effects, and a random effect of centre. A 1.25% significance level will be adopted. The mean difference between the groups will be presented with a 95% confidence interval. Using likelihood methods for estimation, this analysis provided valid results under a missing-at-random (MAR) drop-out pattern [46]. An analogous analysis method will be applied to the prespecified secondary outcome variables, with adjustment for the baseline value of the variable associated with the outcome, rather than baseline TIR. A similar analysis method will be applied to all longitudinally measured and continuous exploratory outcomes. Analysis of cross-sectional continuous outcomes will be performed by a two-sample two-sided t-test or a Mann-Whitney U test in case of skewed distributions. For comparing binary pregnancy outcomes between both groups, a Fisher exact test will be used, whereas a two-sample t-test or Mann-Whitney U test will be used for normally distributed or not-normally distributed continuous pregnancy outcomes, respectively. As a prespecified subgroup analysis, we plan to compare the primary and three key secondary outcomes between women who started the intervention early (screening < 8 weeks) versus later in pregnancy (screening ≥ 8 weeks).

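### Holm's procedure would replace the plan's valid Bonferroni tests at the same 5% family-wise error, with equal or higher power for all four confirmatory outcomes and no extra patients

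*Protocol article*

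**What the plan says.** All references are to the Statistics part of the protocol article.

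- **Sample size, the family.** "The sample size is determined to have about 90% power for the primary and three key secondary outcomes". The four outcomes are TIR, overnight TIR, TBR and overnight TBR.
- **Sample size, error control.** The four calculations were done separately, "considering a Bonferroni correction for multiple testing to guarantee a 5% two-tailed family-wise significance level".
- **Sample size, power.** The stated power is 91% for TBR, 87% for overnight TBR and 97% for overnight TIR. A blinded re-estimation of variances and correlations is planned after about half of the participants are randomised.
- **Data analysis, primary.** After describing the mixed model for TIR: "A 1.25% significance level will be adopted".
- **Data analysis, key secondaries.** "An analogous analysis method will be applied to the prespecified secondary outcome variables". No separate level is given for them; 1.25% follows from the four-outcome Bonferroni sizing.

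The article mentions no step-down, gatekeeping or other rule for passing on unused alpha.

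**The concern.** Under plain Bonferroni each outcome faces 1.25% whatever the other three show. If TIR, overnight TIR and TBR were all clearly positive and overnight TBR came out at p = 0.03, overnight TBR would not be claimed. Under Holm it would be, with the same 5% guarantee.

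What is at stake falls mainly on TBR and overnight TBR. They carry the hypothesis of less hypoglycaemia by day and night, and they have the lowest stated power of the three secondaries. Overnight TBR, at 87%, is already below the target of about 90%.

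**Working it through.** **Inputs (Sample size and Randomisation sections).** "at least 92 patients in total will be randomised", allocated 1:1, so 46 per arm. "Calculations were performed for showing a time-averaged difference between the two groups over four longitudinal measurements". "A correlation of 0.6 was assumed between repeated measurements and a 20% loss to follow-up during the study was anticipated". Differences and SDs in percentage points: TIR 10 and 13; TBR 1.1 and 1.6; overnight TBR 1.6 and 2.5; overnight TIR 15.2 and 18.4.

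**Alpha.** 4 × 1.25% = 5%, so the family-wise level is as stated.

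**Step 1: reproduce the plan's figures.** The SD of a mean of four measurements is SD × √((1 + 3 × 0.6)/4) = SD × 0.8367. The noncentrality is δ = difference / (0.8367 × SD × √(2/n)), with n women per arm. Power is then computed at two-sided 1.25%.

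- *TIR.* The t-based calculation reaches 90.6% at 36 per arm: 72 evaluable, and 72/0.8 = 90. The plan has 92.
- *Secondaries, n = 46.* For TBR, δ = 1.1 / (0.8367 × 1.6 × √(2/46)) = 3.94.

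| Outcome | δ, n = 46 | t-based power | Normal approximation | Plan states |
|---|---|---|---|---|
| TBR | 3.94 | 91.5% | 92.6% | 91% |
| Overnight TBR | 3.67 | 86.6% | 87.9% | 87% |
| Overnight TIR | 4.73 | 98.4% | 98.7% | 97% |

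Gradual loss reaching 20% after the first visit gives 91.6%, 86.7% and 98.5% (normal approximation). The stated powers therefore correspond to no loss or gradual loss. If 20% of women gave no data at all (46 × 0.8 = 36.8 per arm), they would be about 83%, 76% and 95% (t-based).

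**Step 2: why Holm never does worse.** Order the p-values and compare them in turn with 5%/4 = 1.25%, 5%/3 = 1.67%, 5%/2 = 2.5% and 5%, stopping at the first failure. An outcome with p ≤ 1.25% passes, because every smaller p-value also passes its own step. If m nulls are true, the first true null reached is tested at no more than 5%/m, so the family-wise error is at most 5% under any dependence.

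**Step 3: size of the gain if all four planned effects are true.** Simulation with t-based tests. The correlation between the four test statistics is not in the document; it is assumed to lie between 0 and 0.8.

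| Outcome | 46 per arm: Bonferroni → Holm | 36.8 per arm: Bonferroni → Holm |
|---|---|---|
| TIR | 96.7% → 97.9–99.1% | 91% → 94.0–96.5% |
| TBR | 91.5% → 95.9–97.1% | 83% → 90.1–92.4% |
| Overnight TBR | 86.6% → 94.1–95.0% | 76% → 87.3–88.7% |
| Overnight TIR | 98.4% → 98.9–99.6% | 95% → 96.1–98.2% |
| All four | 75.5–83.3% → 91.5–93.4% | 55–70% → 80–86% |

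The normal approximation leaves the pattern unchanged. At 36.8 per arm, for example, its Bonferroni powers are about 85% for TBR and 78% for overnight TBR.

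**Step 4: error rate and a less favourable case.** With no true effects the simulated family-wise error is the same for both procedures: 0.049 at correlation 0 and 0.032 at 0.8. With some true effects Holm stayed at 0.049 or below. No Bonferroni rejection was lost under Holm in any simulated trial. If only TIR truly differs, its power is 92.6% under Bonferroni and 92.7% under Holm (36.8 per arm, normal approximation).

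**The case against.** The strongest reply is that nothing here is wrong. Bonferroni is valid, the four levels add up to 5%, and sizing and primary analysis use the same level. That stands, and a reader who inferred an error or a contradiction would go further than the document allows.

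Four further points deserve weight.

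- **Lower powers.** A reader might infer that the trial has only about 83–85% power for TBR and 76–78% for overnight TBR. Those figures need 20% of women to contribute nothing. The plan states 91% and 87%, and its likelihood-based repeated-measures analysis uses the earlier visits of women who leave part-way. The lower figures are a pessimistic scenario.
- **The 1.25% for the secondaries.** It is written out only for the primary. For the other three it is a reasonable inference.
- **Favourable scenario.** The gains assume that all four effects are true. Holm's first step is still 1.25%, so an outcome that is alone in being different gains practically nothing.
- **The primary's threshold.** Under Holm, TIR at p = 0.04 could be declared positive because the three secondaries had succeeded. Wanting a fixed threshold for the primary is a legitimate preference. However, the present plan already treats the four outcomes symmetrically, and Holm never makes the primary harder to show.

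The blinded sample size recalculation protects power in part, but at whatever size results Holm is still at least as powerful.

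**Conclusion.** The point holds as an efficiency improvement with no cost in patients or in error control. The benefit is largest for overnight TBR: about 7.5 to 8.5 points at 46 per arm, and about 10 to 12.5 points if 20% of women give no data. For TBR it is about 4 to 6 points at 46 per arm (95.9 − 91.5 to 97.1 − 91.5). For the primary it is about 1 to 5 points across both scenarios, and practically nil if only TIR differs.

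The sizes rest on the plan's own effects, SDs and correlation of 0.6, on all four effects being true, and on an assumed between-outcome correlation of 0 to 0.8. That correlation changes the size of the gain but not its direction.

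**What to change.** Before any between-group comparison is made, replace the sentence "A 1.25% significance level will be adopted" with:

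> The primary and three key secondary outcomes are tested with Holm's procedure at a two-sided family-wise level of 5%, and Holm-adjusted p-values are reported.

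Keep 1.25% as the conservative planning level, so that the sample size and the blinded recalculation are unaffected. This also states outright which rule applies to the secondaries.

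The costs are small:

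- The change loosens a rejection rule in an open-label trial whose recruitment is reported as complete, so it must be dated and documented as a protocol or SAP amendment.
- The primary's threshold can then depend on the secondary results.
- Holm has no simple matching simultaneous confidence intervals. The plan already presents 95% intervals, which do not match a 1.25% test either; 98.75% intervals can be added as conservative simultaneous ones.

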#### *Data analysis*

Analyses will be performed according to intention-to-treat as well as per protocol. Clinical and demographic data at baseline will be summarised in a table using frequencies with percentages, mean values with SD or medians with the interquartile range (IQR). A linear mixed model for repeated measurements will be used for the primary outcome analysis, with TIR as response variable, and group, time point of measurement, stratification factors baseline HbA1c and method of insulin delivery, and finally baseline TIR as main effects, and a random effect of centre. A 1.25% significance level will be adopted. The mean difference between the groups will be presented with a 95% confidence interval. Using likelihood methods for estimation, this analysis provided valid results under a missing-at-random (MAR) drop-out pattern [46]. An analogous analysis method will be applied to the prespecified secondary outcome variables, with adjustment for the baseline value of the variable associated with the outcome, rather than baseline TIR. A similar analysis method will be applied to all longitudinally measured and continuous exploratory outcomes. Analysis of cross-sectional continuous outcomes will be performed by a two-sample two-sided t-test or a Mann-Whitney U test in case of skewed distributions. For comparing binary pregnancy outcomes between both groups, a Fisher exact test will be used, whereas a two-sample t-test or Mann-Whitney U test will be used for normally distributed or not-normally distributed continuous pregnancy outcomes, respectively. As a prespecified subgroup analysis, we plan to compare the primary and three key secondary outcomes between women who started the intervention early (screening < 8 weeks) versus later in pregnancy (screening ≥ 8 weeks).

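### The four confirmatory outcomes are tested at 1.25%, but the mean difference is reported with an unlabelled 95% interval, which can exclude zero when the prespecified test fails

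*Protocol article*

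**What the plan says.** The Sample size section of the protocol article treats TIR, overnight TIR, TBR and overnight TBR as one family, "considering a Bonferroni correction for multiple testing to guarantee a 5% two-tailed family-wise significance level". It adds: "The sample size calculation was performed for these four outcomes separately".

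The Data analysis section describes the linear mixed model for TIR and then sets the test level and, in the next sentence, the interval: "A 1.25% significance level will be adopted. The mean difference between the groups will be presented with a 95% confidence interval". For the three key secondary outcomes it says: "An analogous analysis method will be applied to the prespecified secondary outcome variables". The only change named there is that each outcome is adjusted for its own baseline value.

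The article mentions no interval at an adjusted level. It also does not say that the 95% interval is nominal or descriptive, or that it should not be used to judge significance.

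**The concern.** Two adjacent sentences apply different thresholds to the same mean difference. A reader who checks whether the interval covers zero is applying a 5% test, whereas the plan applies a 1.25% test. When p lies between the two, the report shows a result that fails its prespecified test beside an interval that excludes zero, with no note to explain the difference.

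Clinical readers tend to work from the interval, so the interpretation of a confirmatory outcome is at stake. Less hypoglycaemia is part of the trial's stated hypothesis, and at the design effects the two TBR outcomes are the ones most likely to fall in the gap.

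**Working it through.** **Inputs, all from the protocol article.** Sample size section: family-wise level 5% two-sided, Bonferroni, four outcomes; four repeated measurements with correlation 0.6; 20% loss to follow-up; "at least 92 patients in total will be randomised". Randomisation section: "Participants will be randomised 1:1 to either the 780G (intervention) or SoC (control) group", hence 46 per arm. Design differences and SDs in percentage points: TIR 10 and 13; TBR 1.1 and 1.6; overnight TBR 1.6 and 2.5; overnight TIR 15.2 and 18.4.

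**Step 1. Reproduce the test level.** 0.05 / 4 = 0.0125, as stated.

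**Step 2. Confirm that the design used it.** For a time-averaged difference over four measurements, the variance factor is (1 + 3 × 0.6) / 4 = 0.7. With 46 per arm, a two-sided 1.25% level and the normal formula, the powers are:
- TBR: 92.6% (stated 91%)
- overnight TBR: 87.9% (stated 87%)
- overnight TIR: 98.7% (stated 97%)

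All are within 2 points of the stated figures. At a 5% level with 46 per arm they would be 97.6%, 95.6% and 99.7%, which do not match. The design level is therefore 1.25% for the key secondary outcomes too.

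**Step 3. Compare the intervals.** The critical value is 1.960 for a 95% interval and 2.498 for a 98.75% interval. The ratio is 2.498 / 1.960 = 1.274, so the matching interval is 27% wider.

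**Step 4. Find the zone of disagreement.** SE = SD × √0.7 × √(2/n). For TIR with n = 46: 13 × 0.8367 × 0.2085 = 2.268. The 95% interval excludes zero from 1.960 × 2.268 = 4.445 points, and the 1.25% test needs 2.498 × 2.268 = 5.665 points.

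**Step 5. Find the chance of landing there.** At a true difference d, the chance is Φ(d/SE − 1.960) − Φ(d/SE − 2.498). For TIR with n = 46, d/SE = 10 / 2.268 = 4.409, which gives Φ(2.449) − Φ(1.912) = 0.993 − 0.972 = 0.021. If the 20% lost contribute nothing, n = 46 × 0.8 = 36.8.

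| Outcome | SE, n = 46 | Zone in points, n = 46 | Chance at design effect, n = 46 | Same, n = 36.8 | Chance at half the design effect, n = 46 |
|---|---|---|---|---|---|
| TIR | 2.268 | 4.445 to 5.665 | 2.1% | 5.0% | 21.2% |
| TBR | 0.279 | 0.547 to 0.697 | 5.1% | 9.3% | 20.5% |
| Overnight TBR | 0.436 | 0.855 to 1.089 | 7.7% | 12.4% | 19.7% |
| Overnight TIR | 3.210 | 6.291 to 8.018 | 1.0% | 3.0% | 21.0% |

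At half the design effect with 36.8 per arm, the range is 17.9% to 21.1%. With no true difference, the chance is 0.05 − 0.0125 = 3.75% per outcome.

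**Step 6. Joint coverage of four 95% intervals.** It is at least 1 − 4 × 0.05 = 80%. Under independence it would be 0.95⁴ = 81.5%. The overnight measures are part of the 24-hour measures, so the outcomes are correlated and joint coverage should be higher than that.

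**The case against.** The strongest reply is that the plan has a clear decision rule and the interval is not part of it. The 1.25% level decides significance, and the interval is only how the estimate is presented. An outcome with p = 0.03 has failed under this plan, whatever its interval shows. An unadjusted 95% interval is also a valid interval for a single difference, and reporting one beside an adjusted test is common. All of this stands, and it limits the point to reporting.

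It also rules out two stronger readings that a reader might infer. The first is that the intervals break a promised family-wise guarantee. The Sample size section promises a family-wise significance level, which concerns tests; simultaneous coverage is claimed nowhere. The second is that the plan lets a failed outcome be declared positive. No sentence makes the interval a criterion for success. A family-wise error of up to 20% (18.5% if independent) would arise only if someone ignored the 1.25% rule and read all four outcomes from their 95% intervals.

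Two smaller objections also have weight. The interval sentence follows the TIR model directly, so its extension to the key secondary outcomes rests on the analogous-method sentence; that is a reasonable reading, but not an explicit one. And the chances at 36.8 per arm are an upper case for attrition, because a likelihood-based mixed model uses partial data from women who leave early.

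What does not stand is that this is mere detail left to a fuller document. The article states the interval level itself, and that level does not match the test level beside it.

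**Conclusion.** The mismatch is real and of low severity. For 0.0125 < p < 0.05, the reported interval excludes zero although the prespecified test is not significant, and the text does not warn of it. At the design effects the chance lies between 1% and 8% per outcome with 46 per arm, and between 3% and 12% if the 20% lost contribute no data. For the primary outcome, these are about 2% and 5%. It rises to about 20% per outcome if the true effects are half those planned.

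These figures rest on the article's own SDs and correlation, a normal approximation, and no gain in precision from baseline adjustment. A gain in precision would shift the zones to smaller differences. The existence of the gap depends on none of these assumptions.

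A reader might infer that error control has failed, or that the four intervals have only 80% joint coverage. Neither follows: the 1.25% test still controls the family-wise error, and 80% is a worst-case bound. No power or sample-size figure changes.

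**What to change.** In the Data analysis section, replace the interval sentence with one that does three things:
- presents 98.75% confidence intervals for TIR, overnight TIR, TBR and overnight TBR, naming all four so that nothing depends on the analogous-method wording;
- states that significance for these four outcomes is judged only by p < 0.0125;
- labels any 95% intervals also shown for them as nominal and not adjusted for multiplicity.

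Exploratory outcomes can keep 95% intervals. The change should be recorded before between-group results are seen, so that the choice of interval is not driven by the data.

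The cost is one sentence and confirmatory intervals that are 27% wider. No extra participants, data or analyses are needed.

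### As printed, the early-versus-late subgroup analysis compares outcome levels between early and late bookers and does not estimate whether the HCL-versus-SoC effect differs by timing

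*Protocol article*

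**What the plan says.** The last sentence of Data analysis (protocol article, Statistics) sets one prespecified subgroup analysis. It will "compare the primary and three key secondary outcomes between women who started the intervention early" and those who started later. The two sides are defined as "early (screening < 8 weeks) versus later in pregnancy (screening ≥ 8 weeks").

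Three other statements bear on it:

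- The mixed model in the same section lists group, time point, the HbA1c and insulin-delivery strata and "baseline TIR as main effects, and a random effect of centre". It names no timing-of-screening term and no interaction.
- Under Randomisation, "Deterministic minimisation of variation will be used based on the following baseline characteristics: study centre, baseline HbA1c" and method of insulin delivery. Gestational age at screening is not among the factors.
- Under Randomisation, "Participants will be randomised 1:1 to either the 780G (intervention) or SoC (control) group". Under Groups, Control, women in the SoC arm stay on their existing therapy, so they do not start the intervention.

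No other section describes the subgroup analysis differently.

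**The concern.** A subgroup analysis in a randomised trial should ask whether the treatment effect differs between subgroups. The printed sentence compares the outcomes themselves, early against late. Women who book before 8 weeks may differ from later bookers in pregnancy planning, baseline HbA1c or baseline TIR. The contrast cannot separate such differences from an effect of timing.

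If the sentence is followed, better TIR among early starters could be reported as a benefit of starting HCL early even if early bookers on SoC do equally well. A real timing effect could also be hidden by an opposite prognostic difference. The analysis covers all four powered outcomes, so the result is likely to be quoted.

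**Working it through.** **1. What each contrast estimates.** Let late SoC women have mean μ, let HCL add τ in late bookers, let early bookers differ by *a* whatever their treatment, and let HCL add a further δ in early bookers. The question of interest is δ. With equal allocation within strata:

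- Early minus late within HCL: (μ + τ + a + δ) − (μ + τ) = a + δ
- Early minus late, both arms pooled: a + δ/2
- (HCL − SoC in early) − (HCL − SoC in late): (τ + δ) − τ = δ

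Only the last is free of *a*. This holds for any value of *a*.

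**2. Variance inputs, from Sample size.** TIR SD 13, correlation 0.6, four measurements, 92 women, 20% loss anticipated. The SD of a woman's average over four visits is 13 × √((1 + 3 × 0.6)/4) = 13 × 0.8367 = 10.88 points.

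As a check on this formula, I recomputed the plan's own powers at 46 per arm and the level in "A 1.25% significance level will be adopted", two-sided. Noncentral t gives 91.5%, 86.6% and 98.4% for time below range (TBR), overnight TBR and overnight TIR; the plan states 91%, 87% and 97%. The agreement is within 2 points. The plan gives no figure for the subgroup analysis.

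**3. Illustration of the bias.** Assumptions, not in the document: half the women are screened early (23 per cell), all 92 are analysed, there is no covariate adjustment, the HCL effect is 10 points in both strata (δ = 0), and testing is two-sided at 5%. There were 5,000 simulated trials per row.

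| Assumed *a* (points) | Within HCL: mean, significant | Pooled: mean, significant | Interaction: mean, significant |
|---|---|---|---|
| 0 | 0.0, 5% | 0.0, 5% | 0.0, 5% |
| 3 | 2.9, 15% | 3.0, 27% | −0.1, 5% |
| 5 | 5.0, 34% | 5.0, 60% | 0.0, 4% |
| 8 | 8.0, 70% | 8.0, 94% | 0.0, 5% |

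In the reverse case (a = −5, δ = +5), the within-HCL contrast averages 0.1 and the pooled contrast −2.4. The interaction averages 5.1.

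**4. What the replacement can deliver.** With *N* women analysed and a fraction *p* screened early, the interaction SE is 10.88 × √(4/(Np) + 4/(N(1 − p))). The document does not give *p*, so 20% and 50% are shown. Power is at two-sided 5%.

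| N analysed | p | SE (points) | Power for a 10-point interaction | Detectable at 80% power |
|---|---|---|---|---|
| 92 | 0.5 | 4.54 | 60% | 12.7 |
| 92 | 0.2 | 5.67 | 42% | 15.9 |
| 73.6 (20% loss) | 0.5 | 5.07 | 51% | 14.2 |
| 73.6 (20% loss) | 0.2 | 6.34 | 35% | 17.8 |

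First row: 10.88 × √(4/46 + 4/46) = 4.54. Baseline adjustment would narrow these somewhat; the document gives no correlation with baseline from which to say by how much.

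**The case against.** The strongest reply is that the sentence is shorthand. It is introduced as a subgroup analysis, and its operative definition, gestational age at screening, is fixed before randomisation and known in both arms. That fits the usual meaning of a treatment effect by subgroup. A condensed article also commonly leaves interaction terms and covariates to the full protocol or analysis plan, which are not shown. This stands in part: a reader might infer that the analysis is certainly confined to the HCL arm and discards the controls, and the text does not settle that. It does not rescue the sentence, because the article states a contrast rather than staying silent, and both readings of that contrast compare early with late women.

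A second reply is that the mixed model adjusts for baseline value, HbA1c stratum and insulin delivery, which would remove much of the difference if carried over. It would reduce the confounding but not remove it. The sentence does not say that it is carried over. The 10-day baseline recording is also tied to screening, so it falls at different gestational ages in the two subgroups, and the Background section itself says insulin sensitivity varies with gestation.

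A third point cuts against a stronger reading. A reader might infer that the 8-week split is invalid because start dates overlap: run-in begins "within 1 week after screening" and lasts 10 days, and training follows ("Within one week after the run-in phase, participants randomised to the intervention group"). A woman screened at 7w6d could start at 9w2d to 11w2d, and one screened at 8w0d at 9w3d to 11w3d. The arithmetic is right, but women one day apart are alike at any cut-off. The 8-week limit also has a design basis: it decides who has study visit 1 and the 9–12 week recording. It is no ground for criticism here.

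**Conclusion.** The point holds in a limited form. On either reading the printed contrast estimates *a* + δ or *a* + δ/2, not δ. It therefore mixes timing with prognostic differences between early and late bookers and does not show whether the HCL-versus-SoC effect depends on timing. That follows from the wording and from screening time being neither randomised nor a minimisation factor.

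The size of the bias is unknown. The 3 to 8 points in the illustration are assumed, and the document reports no outcome or prognostic factor by booking time. A reader might infer a bias of up to 80% of the 10-point target (8/10). The document does not support that, and the unadjusted false-positive rates rest on the same assumption.

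This should be fixed. It concerns one subgroup sentence to which no confirmatory claim is attached. The primary model, the 1.25% level, the sample size and the key secondary comparisons are unaffected.

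**What to change.** Replace the subgroup sentence with: *The HCL-versus-SoC difference in the primary and three key secondary outcomes will be estimated, with confidence intervals, within women screened < 8 and ≥ 8 weeks, using both randomised arms and the primary mixed model with screening stratum and a group-by-screening-stratum interaction added; the interaction estimate will be reported as exploratory.* For each key secondary outcome, its own baseline value replaces baseline TIR, as already planned. If an analysis plan already specifies this, the published sentence should be brought into line with it.

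The cost is one sentence and no new data, since screening date is held for both arms. The change should be made before the outcomes are analysed, so that it remains prespecified.

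The downside is imprecision. On the SEs above, the 95% interval for the TIR interaction would be about ±8.9 points (1.96 × 4.54) to ±12.4 points (1.96 × 6.34), so a non-significant interaction should not be read as evidence of equal effects. Because timing is not randomised, the interaction would show effect modification by screening time, not that an earlier start causes the difference.
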